## Abstract

The burden of cardiovascular disease (CVD) is diminishing in developed countries. However, in middle- and low-income countries the CVD death rates are growing. CVD is the most common cause of death and disability in Iran and accounts for nearly half of all mortalities in Iranians. Therefore, preventive strategies by risk factor modification are a top priority in the country.

Recently, Mobile-Health (mHealth) technology has been the focus of increasing interest in improving the delivery of cardiovascular prevention, targeting a combination of modifiable risk factors.

This parallel-group single-blinded randomized controlled trial study has been designed to evaluate the impact of using a mHealth application on risk factors control. Individuals aged between 25 and 75 years who have documented CVD by coronary angiography in Tehran Heart Center and have at least one uncontrolled risk factor from the three including hypertension, dyslipidemia, and current cigarette smoking will be included. We are going to randomize 1544 patients into two study arms as follows: 1- Intervention: usual care + mHealth 2- Control: usual care + paper-based recommendations and educational materials. After 3 and 6 months of follow-up, the status of risk factors will be determined through outpatient visits and face-to-face interviews for both arms. Outcome: Successful risk factor control will be measured after 3 and 6 months.

Nowadays, mHealth is becoming increasingly popular, providing a good opportunity for constant monitoring of risk factors and changing health behavior in a target population. Meanwhile, providing evidence for the effectiveness of health intervention delivery using mobile technologies could help health providers encourage their at-risk population to stop smoking, control blood pressure and blood cholesterol, and participate in regular physical activity. While the burden of CVD is growing in developing countries, this type of intervention can be a cost-effective way to reduce it in these countries.

## Introduction

1

Cardiovascular diseases (CVD) remain a significant health concern, especially in middle- and low-income countries like Iran where the mortality rate from CVD is on the rise, despite a decreasing trend in developed countries [1,2]. Preventive strategies have played a crucial role in reducing coronary artery disease (CAD)-related mortality in Europe and the United States, emphasizing the importance of focusing on individual and population-level risk factors [3,4].

In Iran, CVDs are a leading cause of death and disability, accounting for nearly half of all annual deaths [5]. With a large young population transitioning into high-risk CVD age groups in the future, the potential impact on mortality and disability is concerning, especially among productive forces under 55 years old [[6], [7], [8], [9]]. The burden of CVD and its associated risk factors, including cigarette smoking (CS), hypertension (HTN), dyslipidemia (DLP), diabetes, obesity, and inadequate physical activity, poses a significant challenge for healthcare systems in developing countries. Targeted preventive strategies addressing these risk factors and promoting healthy behaviors are essential to reduce mortality and disability from CVD [10]. Given the need for innovative approaches to optimize secondary prevention and treatment goals, Mobile-Health (mHealth) technology has emerged as a promising tool to strengthen preventive efforts in cardiovascular health [11]. Leveraging mobile phone applications or “apps” is a suitable and accessible method for delivering interventions to effectively manage CVD risk factors [12,13].

According to recent literature reviews, mobile-based health interventions have a strong positive effect on lifestyle modification and prompting physical activity and may be used as an adjuvant method among patients with CVD for secondary prevention [14,15].

This manuscript introduces a study on the use of mHealth technology to assist patients with CAD in controlling three key CVD risk factors HTN, DLP, and CS. By developing evidence-based interventions guided by clinical guidelines, this study aims to evaluate the effectiveness of this approach in managing these risk factors in the Iranian population. This research underscores the importance of adopting effective preventive strategies that are widely applicable and implementable to address the increasing burden of CVD in diverse populations.

## Materials and method

2

### Ethical considerations and registration

2.1

Written Informed consent was obtained from each patient before recruitment and the study protocol conforms to the ethical guidelines of the 1975 Declaration of Helsinki as reflected in a priori approval by the institution's human research committee. The study was approved by ethical committees of the Tehran University of Medical Sciences (Ethical code: IR. TUMS.MEDICINE.REC.1399.032). This study was registered in the Iran Randomized Clinical Trial Center with the ID of IRCT20221016056204N1 on March 12, 2023.

### Design

2.3

This parallel-group single-blinded randomized controlled trial study, has been designed to compare the impact of 6 months using an mHealth application and paper-based educational content on risk factors control in CAD patients.

The study protocol is according to the Standard Protocol Items: Recommendations for Interventional Trials (SPIRIT) 2013 Statement [16].

### Study setting

2.4

Tehran Heart Center (THC) is a major academic tertiary-care hospital specializing in cardiovascular disorders in Iran which is affiliated with Tehran University of Medical Sciences with 460 inpatient beds, 11 operating rooms, and 6 active Cath Labs [17]. We will include eligible individuals who have attended the THC for diagnostic and treatment services. Patients should have a history of CAD defined as myocardial infarction, percutaneous coronary intervention, coronary artery bypass graft surgery, or coronary angiography confirming stenosis >50% in at least one of the major epicardial coronary arteries or their main branches in the last 6 months, along with current uncontrolled HTN, uncontrolled DLP, or current CS (The definitions of uncontrolled risk factors are described later in “Definition” section). The diagnosis of CAD is made by expert cardiologists. Given that the application is designed to control risk factors of CAD, individuals entering the study are required to have at least one uncontrolled risk factor to assess the efficacy of the app in improving these factors. Individuals over the age of 75 will not be included in the study due to the potential challenges associated with utilizing mobile technology, as well as individuals under 25 due to their lower likelihood of presenting with CAD. Regarding the 6-month follow-up period, patients who are willing to remain in the study for the entire duration will be included. Considering the potential difficulty of utilizing the application in some older individuals, especially those with low literacy levels, the study sample will be limited to individuals who have the ability and willingness to use the application, either independently or with assistance from a trusted relative they lived with. Due to the difficulty of physical presence in patients with significant morbidity and chronic illnesses, and the challenges in obtaining informed consent from individuals with cognitive impairment, they will be excluded from the study. The mentioned conditions are determined by medical history and/or physician diagnosis.

The details of inclusion and exclusion criteria are listed in Table 1.

**Table 1 tbl1:** Eligibility criteria for the participants.

Inclusion criteria	Exclusion criteria
▪ History of coronary artery disease^a^ ▪ Having at least one uncontrolled risk factor^b^ ▪ Aged between 25 and 75 years ▪ Inclination to stay in the study for 6 months ▪ The participant's (or one of their trustworthy relatives who live with them) having and ability to use a smartphone ▪ Willing to control the risk factors using an application ▪ Provides informed consent to participate in the study	• Mental retardation • Individuals with prohibitive morbidities that require close face-to-face monitoring. • End-stage chronic disease such as hepatic and/or renal failure, heart failure, active cancer

a History of myocardial infarction, percutaneous coronary intervention, coronary artery bypass graft surgery, coronary angiography confirming stenosis>50% in at least one of the major epicardial coronary arteries or their main branches.

b Including uncontrolled hypertension, uncontrolled dyslipidemia, and current cigarette smoking for ≥12 months.

## Intervention

3

### Intervention and control groups

3.1

Hypertensive participants in both arms will be educated on the correct Blood Pressure (BP) measurement method at the baseline face-to-face visit. In the next (3 and 6 months since the randomization) visits, patients in the control group will be asked to bring the paper BP chart of one-week daily home measurements for documentation.

Smoking cessation pamphlets and booklets designed by THC will be presented to smoker patients in the control arm. All patients in the control arm also will receive paper-based lifestyle modification recommendations including a healthy diet and physical activity schedule.

### Green heart application

3.2

The application named “**Green Heart**” can provide individualized treatment for each risk factor according to the current international guidelines. Furthermore, mHealth will supply knowledge for an accurate method of home BP measurement. Thereafter it averages one-week recorded BP and recommends the patient visit the doctor or take drugs at an appropriate time and regulates the time intervals of recommendations concerning the results. Additionally, this app is going to advise about lifestyle modification including low-salt, low-fat, low-sugar, and high-fiber diets, increasing the level of physical activity, weight loss, and quitting smoking. One of our important goals is smoking cessation. To achieve this goal, we have designed an individualized algorithm according to each person's status regarding the level of his/her inclination to smoke, amount of consumption, etc. We are going to reduce the temptation even in patients who will quit smoking by close follow-up. The contents of messages will be approved by related specialists in each section. To develop the application, we will follow 4 steps.1)Planning: Providing and extracting the evidence from the American College of Cardiology/American Heart Association (ACC/AHA), the European Society of Cardiology (ESC), and the National Institute for Care and Excellence (NICE) guidelines and adapting them for the Iranian population by consulting with experts.2)Analysis and designing: Determining the rules for judging criteria and designing the algorithmic diagram for each risk factor.3)Implementation: Installation of database and designed algorithms through coding by an Information Technology (IT) specialist. Data expert software programming will be implemented in two phases. 1-Build a smart short message service robot to interact with target people by sending motivational and inhibitory texts to evaluate the extent of patient coverage; 2- Build a more comprehensive app using the results from step one.4)Evaluation: Revising the app by experts and reflecting on the revisions. To examine the app, initially, we will apply it to our research center personnel and get their feedback. If necessary, we will revise it in the pilot phase. The installation of the software app will be performed on mobile devices of eligible participants by our team. Participants will also be taught how to use the app. To resolve the problems, the patients will be asked to work with this app in the presence of our staff. To respond to any existing questions, we will also give them a telephone number for technical support. Connecting to the internet is not needed during the process of answering questions, and receiving advice and reminders. Whenever the person connects to the internet, the data will be collected and saved to the server.

#### Use of guidelines in the development of the app

3.2.1

When developing the app, we will incorporate the following guidelines into the algorithm of the app.•ESC Guidelines on prevention of DLP [18].•ACC/AHA Guideline on arterial HTN [19].•NICE smoking cessation guideline [20].

These guidelines will be converted into computer-interpretable functions and applied to assessment and feedback systems.

#### How does the green heart app work?

3.2.2

1.Providing condition-specific education, presenting easily-understandable information, customized to each patient, and enforcing behavior change.2.Providing education using different modalities (multimedia, text, interactive material) to reinforce teaching.3.Providing a means of continuous feedback to find out what the patient already knows,And what they have learned and correct any misinformation.4.If applicable, track progress towards goals, for example in the case of smoking cessation support.

#### Contents of the green heart app

3.2.3

The app will consist of 3 modules, each designed to address a specific risk factor.1Smoking2.HTN3.DLP

### The module of the app which targets smoking cessation includes the following features

3.3

•Questionnaires to track the status of the patient: Baseline and follow-up forms (assessment of the degree of nicotine dependence by Fagerström test [21], the duration of smoking, the frequency of quitting, the daily cost of smoking, the use of hookah, the state of the desire to smoke, and the reason for the desire to smoke)•Stream of educational content on the risks of smoking, benefits of quitting, techniques and tips on how to cope with cravings and withdrawal•Stream of supporting messages: Motivational messages (e.g., The effect of quitting on improving health and the amount of recovered cost in case of complete smoking cessation), encouraging, and warning messages•Quit plan builder: The personalized quit plan builder, Automated messages and feedback to help the patient follow the plan, a Visual timeline for viewing progress•Features to increase adherence to the app include an easy tutorial to familiarize the patient with the main app features and push notifications to keep the patients in touch with the app even when the app is closed.

### The module of the app which targets HTN includes the following features

3.4

•Educational information to improve knowledge of HTN: Offering info about the risks of consequences of uncontrolled HTN and benefits of managing HTN, selecting an appropriate sphygmomanometer, guidance to choosing the size of the BP cuff according to the size of the arm circumference and standard technique of measuring BP•Educational information to improve lifestyle: Offering info on how lifestyle changes can help lower BP and reduce the risk of heart disease•Support for Self-monitoring of BP: Patients log their BP twice a day, seven days a week (using an input form with the possibility for refresh/reinsertion of information) according to the guidance of entering systolic and diastolic BP based on the monitor screen of the digital device, App keeps track of systolic and diastolic BP and shows trends with graphs and charts. Patients can view trends of their BP over time. Automatic feedback on the entered values by using color codes for specific ranges and showing alerts is provided.•Reminder functionality for improving medication adherence: Setting reminders to take medications at a specific time.

### The module of the app which targets DLP includes the following features

3.5

•The educational content on the subject of DLP: Info about the risks and consequences of uncontrolled DLP and benefits of managing DLP•Educational content for a healthy lifestyle: Info on how a healthy lifestyle can help reduce lipid levels and decrease the risk of heart disease and heart attacks•Reminder functionality for improving medication adherence: Setting reminders to take medications at a specific time•Support for self-monitoring of Low-density Lipoprotein Cholesterol (LDL-C): A space for entering the number of LDL-C according to the picture guide based on the patient's lab test sheet is provided. After the user enters the LDL-C, questions about the type of DLP medication (statin/ezetimibe) and its dose will be asked, and if the entered number is higher than the target, a corresponding message will be sent to him/her about the necessity of referring to the doctor for increasing the dose of the medication or to add another category of medication and if it is normal, it is recommended to continue the drug and do a lab test again after 12 months.

#### How the patients should use it?

3.5.1

To utilize the app, participants need to have a smartphone and internet access, although the final product may include some offline features as well. Patients consume teaching material and send feedback. Ideally, the user will open and use the program several times a day.

#### How to measure application adherence?

3.5.2

To measure patient engagement, we're going to assess both frequencies and the intensity of app usage: The frequency of app usage will be measured by logging “system-usage” data (the number of logins will be recorded per participant). The intensity of usage will be measured by recording the number of viewed pages and several filled-out self-report questionnaires.

### Study outcomes

3.6

**Primary outcome:** Successful risk factors’ control measured at 3 and 6 months after randomization.

This outcome will be categorical as follows.1No controlled risk factors2One controlled risk factor3Two controlled risk factors4Three controlled risk factors

**Secondary outcomes**: Includes risk factors control in each level of stratification (7 levels presented early in the method section).1Number of participants who remain active users of the app till to the end of the intervention.2Controlled CS3Controlled HTN4Controlled DLP5Controlled CS + HTN6Controlled CS + DLP7Controlled HTN + DLP8Controlled HTN + DLP + CS

The definition of being controlled for each risk factor is presented in the “Definitions” section. Each risk factor that meets the outcome will be regarded as a successful intervention.

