### Randomization and implementation

3.10

Randomization will be performed at 7 different levels based on the type and number of risk factors the patients have (stratified randomization). Participants will be categorized into the following 7 levels; 1) Only CS, 2) Only HTN, 3) Only DLP, 4) CS + HTN, 5) CS + DLP, 6) DLP + HTN, 7) CS + HTN + DLP.

Participants in each level will be randomized into two study arms as follows.1Intervention (case) arm: Usual care + mHealth2Control arm: Usual care + paper-based recommendations and educational materials

In each level, participants will be assigned into two arms by block randomization with a 1:1 allocation using variable block sizes of 2, 4, 6, 8, and 10. Allocation of each subject to the study arms will be performed online to prevent selection bias and respect allocation sequence concealment (By concealing the allocation sequence). Allocation of each participant will be performed, just after inclusion and exclusion criteria are met and informed consent is signed by the participants. Computer-generated random number list will be utilized using permuted block stratified randomization. (Block stratified randomization Windows Version 6.0, by Steven Piantadosi, M. D., Ph.D., Cedars-Sinai Medical Center).

The practitioners who evaluate the risk factors controlling status are blinded to the group assignment.

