### Statistical methods

3.12

Continuous variables will be presented through mean with the standard deviation (SD) for normally distributed variables or median with the interquartile range boundaries for skewed variables. Categorical variables will be presented as the frequency with percentage. To check the normality distribution of continuous variables, histograms will be applied along with the above descriptive quantities. Risk factors’ status will be measured at different time points to determine the final status at the end of certain time points. We will compare the prevalence of the controlled risk factors in time points of 0 (baseline), 3 and 6 months between intervention and control groups using x^2^ tests at each point. Multivariate logistic regression analysis will be used to determine the effect of the intervention on the control of risk factors at the end of 6 months. The effect will be reported as Odds Ratios with the corresponding 95% confidence interval. This will be a per-protocol approach. To perform the intention-to-treat method, participants will be analyzed according to the group they were allocated not the actual intervention they received. The missing values for subjects who were lost to follow-up or did not cooperate until the end of the study will be evaluated to see to what extent the missing data are completely random. If missing data do not violate the randomness assumption, they will be replaced using the multivariate missing imputation method. Otherwise, stratified analysis and sensitivity analysis for missing data will be considered. Finally, the size of the effect is measured and reported as a relative risk/risk ratio with a corresponding 95% confidence interval. The effect will be calculated and reported as a hazard ratio with the corresponding confidence interval.

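### The 0–3 primary outcome at two unranked visits has no designated test: the planned chi-square tests and logistic model analyse something else

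*Protocol article*

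**What the plan says.** **Outcome (section 3.6).** The primary outcome is "Successful risk factors’ control measured at 3 and 6 months after randomization". Of its scale the article says "This outcome will be categorical as follows", and lists none, one, two or three controlled factors. The same section closes with a second success rule: "Each risk factor that meets the outcome will be regarded as a successful intervention".

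**Entry and allocation (Table 1 and section 3.10).** Patients qualify by "Having at least one uncontrolled risk factor", so they enter with one, two or three. "Randomization will be performed at 7 different levels based on the type and number of risk factors the patients have (stratified randomization"; within each level "participants will be assigned into two arms by block randomization with a 1:1 allocation".

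**Analysis (section 3.12).** "We will compare the prevalence of the controlled risk factors in time points of 0 (baseline), 3 and 6 months between intervention and control groups", by chi-square test at each time. A multivariate logistic regression then estimates the effect at the end of 6 months and is described as per-protocol; an intention-to-treat approach follows. An odds ratio, a risk ratio and a hazard ratio are each announced as the effect. The section mentions stratified analysis only as an option for handling missing data.

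**The concern.** A four-level ordered outcome calls for an analysis on that scale, at one named time. A comparison of prevalences is a comparison of proportions, and a binary logistic model needs a cut that the article does not give. It could be at least one factor controlled, all entry factors controlled, or each factor separately. With two visits, two success rules, several possible cuts, two analysis sets and three effect measures, nothing identifies the result that decides the trial.

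The scale is also incomplete. If only factors uncontrolled at entry are scored, the stratum sets the highest attainable count: one in levels 1–3, two in levels 4–6, three in level 7. A patient whose only factor is smoking and who quits then gets the same score as a three-factor patient who fails on two. An analysis that ignores the strata mixes these cases.

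**Working it through.** **1. Outcome and analysis side by side**

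| Element | Section 3.6 | Section 3.12 |
|---|---|---|
| Scale | four ordered levels | prevalence; undefined binary event |
| Time | 3 and 6 months, unranked | chi-square at 0, 3 and 6; logistic at 6 |
| Analysis set | – | logistic per-protocol; intention-to-treat also described |
| Effect measure | – | odds, risk and hazard ratio |
| Strata | secondary outcomes by level | in no named comparison of arms |

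The hazard ratio has no time-to-event outcome behind it.

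**2. The plan's own sample size.** Smoking drives it: 0.08 against 0.12 (Table 3), α = 0.05, power 80%, 10% loss.

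n = [z(α)·√(2·0.10·0.90) + z(β)·√(0.08·0.92 + 0.12·0.88)]² / 0.04²

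With z(α) = 1.645 and z(β) = 0.842 this gives 695, and 695/0.9 = 772.2, against the stated 772. It reproduces with one-sided α (two-sided gives 980), which is a separate matter. Two things count here: about 695 evaluable patients per arm, and a size based on single-factor proportions, not on the 0–3 count.

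**3. Highest attainable count.** Assumptions: the Table 3 shares (dyslipidaemia 0.72, hypertension 0.47, smoking 0.34) describe uncontrolled factors and are independent, and only entry factors are scored.

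- At least one factor: 1 − 0.28·0.53·0.66 = 0.902
- Exactly one: (0.0505 + 0.0869 + 0.2519)/0.902 = 43%
- Exactly two: (0.0447 + 0.1297 + 0.2233)/0.902 = 44%
- All three: (0.72·0.47·0.34)/0.902 = 0.1151/0.902 = 13%

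**4. Expected outcome.** Applying the Table 3 success rates within strata:

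| Controlled | 0 | 1 | 2 | 3 |
|---|---|---|---|---|
| Control | 76.7% | 21.9% | 1.3% | 0.02% |
| Intervention (1.5-fold) | 66.0% | 30.9% | 3.0% | 0.08% |

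The top category holds about 772·0.000224 = 0.2 control and 772·0.000758 = 0.6 intervention patients, so it is practically empty.

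**5. Size of a single test.** Simulation under no effect, with 695 per arm, 1:1 allocation within strata, two-sided 0.05 and 4000 runs per setting: four-category chi-square 3.6–4.8%, binary chi-square (at least one controlled) 4.4–4.9%, stratified mean-score test 4.7–5.4%.

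**6. Two visits.** If a win at either visit at 0.05 counted:

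- independent tests: 1 − 0.95² = 9.75%
- bivariate normal, correlation 0.3 to 0.7: 9.5% to 8.4%
- simulated pairs of four-category tests, latent correlation 0 to 0.95: 9.0% to 7.1%

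**7. Power at month 6** (simulated, 695 per arm, two-sided 0.05, same risk ratio for every factor)

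| Risk ratio | Four-category chi-square | Binary chi-square | Stratified mean-score |
|---|---|---|---|
| 1.2 | 36% | – | 50% |
| 1.25 | 50% | 63% | 66% |
| 1.3 | 70% | 78–80% | 83% |
| 1.5 (planned) | 99% | 99% | above 99% |

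**8. Month 0.** If only entry factors are scored, every patient's count is zero at baseline. If absent factors are scored as controlled, the baseline count is fixed by the stratum, which allocation balances. The test tells nothing under either rule.

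**The case against.** A reader might infer that ignoring the strata makes the planned tests invalid. The documents do not support that. Allocation is 1:1 in blocks within each level, so the caps are balanced between arms, and each chi-square test keeps its size at or slightly below 5%.

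A reader might also infer a serious loss of power. At the planned 1.5-fold effect there is practically none. The article speaks of prevalences, "between intervention and control groups using x^2^ tests at each point", which reads more naturally as a binary comparison than as a four-category table, and the binary version loses only about 3 to 5 points at a risk ratio of 1.3.

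Three further premises are inferences:

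- The logistic covariates are not listed, as is common in an article, and may include the strata. Section 3.6 also lists control by stratification level among the secondary outcomes.
- No rule says that each visit is tested at 0.05 or that either may win. The logistic model is placed at 6 months, which points to that visit.
- The scoring of factors absent at entry is not stated. The definition of controlled dyslipidaemia, which requires a reduction from baseline, supports the cap but does not settle it.

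All of this stands and limits the size of the point. What remains is conflicting text and not detail left to an analysis plan: a four-level outcome with analyses that do not fit it, two unranked visits, three effect measures, and a per-protocol label on the effect model.

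**Conclusion.** The point holds as a mismatch between the declared primary outcome and the stated analyses, with no single primary visit, test, cut or effect measure named. It does not hold as a claim that any one chi-square test is invalid.

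The main cost is freedom to choose the primary result after seeing the data. The 7–10% false-positive risk quantifies only the choice of visit, and only under an either-visit rule that the article neither states nor excludes. The second cost is power at effects below the planned one: about 13 points at a risk ratio of 1.3 for the four-category chi-square, and much less for a binary one. The stratum split and the power figures rest on independent factors, Table 3 shares read as uncontrolled factors, a common risk ratio, and scoring of entry factors only.

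**What to change.** In sections 3.6 and 3.12:

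1. Name month 6 as the single primary time point and month 3 as secondary.
2. Define the outcome as the number of factors uncontrolled at entry that are controlled at month 6, and state how it relates to the single-factor success rule.
3. Make the primary test one intention-to-treat Cochran-Mantel-Haenszel mean-score test (or van Elteren test) stratified by the seven levels. Patients are then compared only with others who have the same attainable count.
4. Report one matching effect measure with its 95% confidence interval, for example the stratum-weighted difference in mean count.
5. Adjust the single-factor comparisons for stratum.
6. Drop the month-0 test and the hazard ratio, and make the per-protocol analysis supportive.

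Proportional-odds regression with stratum main effects is less suitable: it cannot represent categories that are impossible in levels 1–6. Collapsing categories once they prove sparse would be a data-driven choice.

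The cost is wording. The strata are already recorded, and no further patients or measurements are needed. Month 3 loses co-primary status, and section 3.9 should say that the trial was sized on single-factor rates and not on the primary count.

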### Sample size calculation

3.9

Farkouh et al. [22] which studied pooled data obtained from large randomized trials display the success rate in controlling risk factors in CAD patients for secondary prevention through lifestyle modification and drug consumption.

To increase the success rate percentage of modifying the risk factors by at least 1.5 times, concerning significance level of α = 0.05, study power of 80% and 10% loss of samples, a sample size of 257, 538, and 772 were considered for DLP, HTN, and CS, respectively. The largest sample size of 772 which is related to CS was selected (772 × 2 = 1544). The calculation was performed by G-power software. The final results are reported in Table 3.

**Table 3 tbl3:** Success rates in controlling Dyslipidemia, Hypertension and smoking and calculated sample size.

Risk Factor	Success rate percentage in the control group	Success rate percentage in the intervention group	Sample size in each group counting 10% shedding of samples	The abundance of patients referred to the Tehran Heart Center
**Dyslipidemia**	0.2	0.3	257	0.72
**Hypertension**	0.11	0.165	538	0.47
**Cigarette smoking**	0.08	0.12	772	0.34

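### Read literally, the secondary outcomes compare control of each risk factor within single stratification levels, although each factor is present in four of the seven levels

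*Protocol article*

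**What the plan says.** Section 3.6 (Study outcomes) introduces the secondary outcomes with "risk factors control in each level of stratification (7 levels presented early in the method section". The list has eight items. The first is the number of continuing app users. The other seven are control of CS, HTN and DLP singly, in the three pairs, and all together.

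Section 3.10 (Randomization and implementation) gives the levels: "1) Only CS, 2) Only HTN, 3) Only DLP, 4) CS + HTN, 5) CS + DLP, 6) DLP + HTN, 7) CS + HTN + DLP". They are mutually exclusive, and items 2 to 8 in Section 3.6 match them one for one.

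Section 3.12 (Statistical methods) compares the proportion with controlled risk factors "between intervention and control groups using x^2^ tests at each point", at 0, 3 and 6 months, and plans a logistic regression at 6 months. It does not mention levels.

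Section 3.9 (Sample size calculation) works factor by factor. It uses "significance level of α = 0.05, study power of 80% and 10% loss of samples", a 1.5-fold increase in success, and the largest result: "The largest sample size of 772 which is related to CS was selected (772 × 2 = 1544"). Table 3 also gives the share of the centre's patients with each factor: DLP 0.72, HTN 0.47, CS 0.34.

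**The concern.** Smokers are in levels 1, 4, 5 and 7, hypertensive patients in 2, 4, 6 and 7, and dyslipidemic patients in 3, 5, 6 and 7. If controlled CS is an outcome of the CS-only level, smokers in the other three levels do not contribute to it. The same holds for HTN and DLP.

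The primary outcome only counts how many factors are controlled, so it cannot show which factor the app improves. Among the listed outcomes, only items 2 to 8 can. Defined by level, each rests on a fraction of the relevant patients, and the joint outcomes may be too sparse for the chi-square test that Section 3.12 names.

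**Working it through.** **Reproducing the plan's figure.** Inputs are the Table 3 success rates (control, intervention): DLP 0.20, 0.30; HTN 0.11, 0.165; CS 0.08, 0.12. With p̄ the mean of the two rates,

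n per arm = [z_α √(2p̄(1−p̄)) + z_β √(p₁(1−p₁)+p₂(1−p₂))]² / (p₂−p₁)², then divided by 0.9.

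- One-sided 0.05: 230.8, 483.7 and 694.5, which become 256.4, 537.5 and 771.7. Rounded up, these are the stated 257, 538 and 772.
- Two-sided 0.05: 293.2, 614.2 and 881.8, which become 325.7, 682.5 and 979.8. These do not match.

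The figures below use two-sided 0.05, because the plan names chi-square tests and 95% intervals. One-sided values are also given.

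**Level sizes.** The documents give no overlap between factors. Assumption: the Table 3 shares are independent, rescaled to patients with at least one factor, 1 − 0.66 × 0.53 × 0.28 = 0.902. Analysed per arm: 772 × 0.9 = 694.8.

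- CS only: 0.34 × 0.53 × 0.28 / 0.902 = 0.056, so 39 per arm. All with CS: 0.34 / 0.902 = 0.377, so 262.
- HTN only: 0.47 × 0.66 × 0.28 / 0.902 = 0.096, so 67. All with HTN: 0.521, so 362.
- DLP only: 0.72 × 0.66 × 0.53 / 0.902 = 0.279, so 194. All with DLP: 0.798, so 555.

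**Power.** Φ{[(p₂−p₁)√n − z √(2p̄(1−p̄))] / √(p₁(1−p₁)+p₂(1−p₂))}

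| Factor | Single-factor level, two-sided (one-sided) | All with the factor, two-sided (one-sided) |
|---|---|---|
| CS | 8.5% (14.5%) | 33% (45%) |
| HTN | 15% (23.5%) | 58% (69%) |
| DLP | 62% (74%) | 97% (99%) |

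**Range without independence.** Take the Table 3 shares as those of enrolled patients, each with at least one factor. CS only and HTN only can then each be 0 to 1 − 0.72 = 0.28 of patients. DLP only can be 1 − 0.34 − 0.47 = 0.19 up to 1 − 0.47 = 0.53. After loss, two-sided power is:

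- CS only: at most 195 per arm, up to 26%.
- HTN only: at most 195 per arm, up to 35%.
- DLP only: 132 to 368 per arm, 47% to 88%.

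On this same basis, all patients with the factor number 236, 327 and 500 per arm, with power 30%, 53% and 96%.

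**Joint outcomes.** Expected successes per arm after loss are level size × joint rate. The joint rate is the product of the single rates if success is independent across factors, and the smallest single rate if it is fully dependent. The chi-square expected success count per arm is the mean of the two arms.

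| Level | n per arm | Independent, control / intervention (mean) | Fully dependent, control / intervention (mean) |
|---|---|---|---|
| CS+HTN | 34 | 0.3 / 0.7 (0.5) | 2.8 / 4.1 (3.4) |
| CS+HTN+DLP | 89 | 0.2 / 0.5 (0.3) | 7.1 / 10.6 (8.9) |
| CS+DLP | 100 | 1.6 / 3.6 (2.6) | 8.0 / 12.0 (10.0) |
| HTN+DLP | 172 | 3.8 / 8.5 (6.2) | 18.9 / 28.4 (23.7) |

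The CS-only level gives 39 × 0.10 = 3.9 expected successes per arm, also below the usual threshold of 5.

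**The case against.** **The text is not explicit that tests run by level.** Section 3.12 names no level for its chi-square tests, the list in Section 3.6 does not use the word only that marks the single-factor levels in Section 3.10, and Table 3 sizes by factor. A pooled analysis may have been meant. This stands as a limit on what can be said: level-wise chi-square testing follows only from combining two sections. But the level is the only denominator Section 3.6 names, so the wording still needs correcting.

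**Low power here is not an error.** These are secondary outcomes and the plan claims no power within levels. That is right, and it limits the weight of the point.

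**Splitting is only part of the cause.** Even with pooling, CS has 33% and HTN 58%, because 772 per arm was set as if every patient smoked. This also stands.

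**Stronger readings to avoid.** A reader might infer that all joint outcomes have expected counts below 1. Under independent success only CS+HTN and all three do so, HTN+DLP averages about 6, and with full dependence none is below 1. The app and the advice address several factors together, so some dependence is plausible. A reader might also infer a 51% chance of a false positive from seven levels at two visits (1 − 0.95¹⁴). That treats two visits by the same patients as independent. Seven independent levels at one visit give 1 − 0.95⁷ = 30%; 51% is an upper limit over two visits. The documents support neither as a firm figure.

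**Conclusion.** The point holds as a poor choice of analysis set that should be changed; it does not invalidate the trial. For CS and HTN, level-wise power is low under any overlap the Table 3 shares allow. For DLP it depends on the overlap and may be adequate. Pooling multiplies power by almost four for CS and HTN and takes DLP well above 80%.

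The chi-square test is unreliable for CS+HTN, CS+DLP and all three if success is independent across factors. With full dependence, CS+HTN is the only joint outcome still below 5. The power figures rest on the Table 3 rates being achieved, 10% loss and two-sided 0.05. The exact values also rest on independent prevalences.

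**What to change.** In Section 3.6, define controlled CS, HTN and DLP among all randomised patients with that factor uncontrolled at baseline (CS: levels 1, 4, 5, 7; HTN: 2, 4, 6, 7; DLP: 3, 5, 6, 7). In Section 3.12, compare arms for these three outcomes with adjustment for level. Present level-specific and joint results descriptively with confidence intervals, using an exact method where expected counts are below 5.

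The change is to wording only: same patients, visits, data and stratified randomisation. The cost is that level-specific results become descriptive. It does not bring CS or HTN to 80% power; that belongs to the sample size in Section 3.9 and needs its own answer.
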